### 2.9. Monitoring

A data monitoring committee will be set up before commencing the protocol, comprising members of the University of Almería. Statistical analyses will be carried out in strict confidence. Based on the data monitoring committee’s advice, the trial’s multidisciplinary group members, together with the cardiologist, will decide whether or not to modify the trial intake.

An adverse event will be considered any untoward medical occurrence involving a subject, regardless of the possibility of a causal relationship. Adverse events will be registered from the moment the subject has signed the written consent. If the adverse event occurs after the subject has signed the informed consent but has not yet started the intervention, it will be considered as not related to the study’s exercise program. If the adverse event occurs after the subject has finished the intervention, it will likewise not be considered to be caused by the study protocol procedure. For this study, sickness, loss of consciousness, weakness, chest pain, or other acute pain will be considered serious adverse events.

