### 2.3. Interventions

To implement this protocol, it will be necessary to include a physical exercise graduate in the multidisciplinary group (described in Section 2.1), who will design and conduct the intervention. This will ensure that patients are controlled, monitored, and directed by a specialist at all times, thus guaranteeing the safety of the protocol and optimizing the intervention.

The intervention program will be conducted over a period of 8 weeks, with three one-hour sessions/week. Every session will comprise a warmup, the main intervention, and a cooldown. The warmup and cooldown will last 10–12 min, respectively, and will be based on the dynamic mobilization of the main muscle groups, especially those of the lower body, to prepare and recover them, respectively, for the main part of the intervention. In the main part, lasting 30–35 min, aerobic-based exercise will be implemented. To reduce mechanical limitations while carrying out the exercise, both a treadmill and a cycloergometer will be used, rotating them weekly, as recommended by a recent meta-analysis [34]. Motivational strategies, such as playing music during the session and giving messages of encouragement, will be used by the professionals supervising the activity. The periodization of the intervention will include two training periods: a two-week familiarization period (FP) and a 6-week training period (TP). The FP will be common to both groups and will be used to increase the training intensity gradually to prepare the patients for the high-intensity TP. In the TP, each group will carry out the corresponding intervention. The HIIT-G group will train according to a predefined high-intensity training program. Taking into account that VO_2_ can be improved either with short or long HIIT intervals [9] and that patients are expected to be in poor physical condition, short training intervals of 1′30′′ will be combined with active rest periods. In each session, the work time at the determined intensity will be at least 50% of the total work interval. The training interval intensity will be gradually increased as the rest periods are reduced. In accordance with Taylor et al. (2017) [35], both the maximal heart rate and the subjective perception of effort will be controlled. The HIIT-G training periodization is presented in more detail in Table 1.

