The training prescribed to the HRV-G group will depend on the subjects’ daily HRV and will follow the HRV-training schema designed by Kiviniemi et al. (2007) [36] (Figure 1). The HRV registration procedure and analysis are described by Carrasco-Poyatos et al. (2020) [37], although, in accordance with the results from recent randomized controlled trials [38,39] and the characteristics of the sample, only high or low intensity will be considered for the present protocol.

The assigned study intervention will be modified or discontinued if the drug dose changes in response to harms, the participant requests it, the disease worsens, or the cardiologist recommends it. Compliance with the exercise protocol will be controlled by the nurse.

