### 2.4. Outcomes

The primary outcome of this study will be the peak oxygen uptake (VO_2peak_) obtained in an incremental treadmill test. The secondary outcomes will be treadmill endothelial and work parameters; heart rate variability; functional parameters; relative weight and body fat distribution; quality of life; inflammatory markers; cognitive function; and exercise adherence, feasibility, and safety. The treadmill test and blood sample collection will be carried out by the cardiologist one week before and after the intervention. Data on functional performance, relative weight and body fat distribution, quality of life, and cognitive function will be recorded by the multidisciplinary group during the first and last weeks of the exercise intervention. Heart rate variability, exercise adherence, feasibility, and safety will be recorded daily during the intervention by the physical exercise graduate.

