#### 2.4.1. VO_2peak_

In accordance with the Spanish Cardiology Society, a modified version of the Bruce protocol will be used as the treadmill test, as it is indicated for elderly people and those considered high risk. Unlike the Bruce protocol, in the modified version, stage 1 starts at a 0% gradient, walking at 45.5 m/min. During stages 2 and 3 (at 3′ and 6′), the percentage gradient increases by 5% each time. Therefore, 6′ more exercise is performed at low intensity. From there, the percentage gradient will increase by 2% every 3′, and the walking speeds will be 67 m/min, 91 m/min, 112.5 m/min, and 136.8 m/min in Stages 4–7, respectively [40]. Pulmonary gas exchange will be measured from the beginning of the rest period until the end of the test using a metabolic system (Parvo TrueOne 2400, ParvoMedics Inc., East Sandy, UT, USA or MetaMax3B, Cortex Biophysik, GmbH, Leipzig, Germany). Prior to the test, participants will be asked to avoid exercise, caffeine, and tobacco for 24 h and food for 2 h but to take all the usual medications. In accordance with Taylor et al. (2017) [41], VO_2_peak will be determined from the average of the two highest values attained in 10 s periods, disregarding outliers when the difference between the two highest VO2 values is greater than 200 mL/min divided by the participant’s body weight. Additionally, an electrocardiogram recording will be taken during the rest period and during the test. Endothelial parameters, such as systolic and diastolic blood pressure and heart rate, will be recorded during the rest period and during the 1 min and 5 min post tests. Work parameters, such as the protocol stages performed, the maximum velocity and gradient reached, the test duration, and the reason for ending it will also be recorded.

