#### 2.4.8. Exercise Adherence, Feasibility, and Safety

Adherence will be assessed by the number of sessions completed by the participants. At least 80% of sessions should be completed to consider adherence successful. Feasibility will be considered compliance with the exercise protocol and will be recorded as the percentage of participants that finish every training session. Safety will be measured as the number of adverse events occurring during the training sessions. In accordance with Villelabeitia-Jaureguizar et al. (2017) [54], these will be recorded as mild, moderate, or severe. Moreover, their relation to the exercise session will also be taken into account. All these variables will be recorded by the multidisciplinary group present at the exercise sessions.

The time schedule for enrolment, interventions, and assessments is shown in Figure 2.

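### Section 2.9 labels every adverse event after the end of training as not caused by a study procedure, although the treadmill post-test and blood draw take place in that period

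*Protocol article*

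**What the plan says.** Section 2.9 defines an adverse event without regard to cause and registers events from signed consent onwards. It then fixes relatedness by timing at both ends of the training programme:

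- An event after consent but before training: "it will be considered as not related to the study’s exercise program".
- An event at the other end that "occurs after the subject has finished the intervention, it will likewise not be considered to be caused by the study protocol procedure".

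Section 2.3 says what the intervention is: "The intervention program will be conducted over a period of 8 weeks, with three one-hour sessions/week". Section 2.4 places the main assessments outside it: "The treadmill test and blood sample collection will be carried out by the cardiologist one week before and after the intervention". The same section makes the primary outcome the VO2peak "obtained in an incremental treadmill test", and section 2.4.1 adds that "the maximum velocity and gradient reached, the test duration, and the reason for ending it will also be recorded".

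Section 2.4.8 defines the safety outcome as the number of adverse events in training sessions, graded by severity, and says of those events that "their relation to the exercise session will also be taken into account".

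**The concern.** Before training has started, an event cannot have been caused by training, so the pre-intervention rule is sound as far as it goes. The post-intervention rule lacks that logic, because effects can follow their cause. It also uses a broader term: it clears the study protocol procedure, not only the exercise programme. Yet a study procedure, the treadmill post-test, is carried out in exactly the period the rule covers.

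The protocol treats the treadmill test as carrying some risk. Section 2.2 excludes patients with contraindications to it, and section 2.4.1 chooses a version meant for elderly and high-risk people and records an electrocardiogram throughout. Section 2.9 itself lists chest pain and loss of consciousness as serious. A patient with either of these on the treadmill at the post-test would have a serious adverse event during a study procedure, recorded by rule as not caused by one.

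At stake is whether the trial's account of harm can be trusted for the post-test and for the time between the last session and that test. Safety is a named secondary outcome, and hypothesis (ii) in the Introduction is that HRV-guided training is safer.

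**Working it through.** No figure in the plan bears on this point, so the check sets the sections against one another along the patient's timeline.

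**Inputs**
- Length of training: 8 weeks at 3 sessions per week (section 2.3), so 8 × 3 = 24 sessions, as in Table 1.
- Treadmill test and blood draw: one week before and one week after training (section 2.4).
- Planned patients: 30 + 30 = 60 (section 2.5).
- Relatedness rules: section 2.9. Safety count: section 2.4.8.

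**Timeline**

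| Time of event | Study activity that could be the cause | Label fixed by section 2.9 | In the section 2.4.8 count? |
|---|---|---|---|
| Consent to first session, including the pre-test | Pre-test, blood draw | Not related to the exercise programme; relation to the test left open | No |
| During a training session | Training | None fixed | Yes |
| Between sessions, during the 8 weeks | Training | None fixed | No |
| After session 24, before the post-test | Training (delayed effect) | Not caused | No |
| During or after the post-test | Post-test, blood draw, training | Not caused | No |

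**Reasoning**
1. Rows 1 and 5 contain the same treadmill test. An event in the first test can be attributed to the test; an event in the second cannot. The only difference is the wording of two adjacent rules.
2. Rows 3 and 4 differ only in whether another session is still to come. An event on the day after session 23 may be judged related to training. The same event on the day after session 24 may not. In HIIT-G, Table 1 puts weeks 7 and 8 at its highest listed work intensity, so session 24 belongs to the most demanding block.
3. The last column shows what the rule leaves untouched. Rows 4 and 5 are outside the in-session count whatever their label, so changing the label does not change that count.

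**Extent**
One test before and one after gives at most 60 × 2 = 120 treadmill tests. Half of them, up to 60, fall under the post-intervention rule, as does the week or so before each. The article gives no adverse event rate, so an expected number of mislabelled events cannot be derived.

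The functional, quality-of-life and cognitive assessments are scheduled in the first and last weeks of training. The conflict over test procedures therefore concerns the treadmill test and the blood draw.

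**The case against.** The best counter-argument is linguistic. The disputed sentence says that the event will likewise not be attributed, which points back to the preceding rule about the exercise programme. On that reading the study protocol procedure is a loose synonym for training, and a post-test event could still be attributed to the test. The reading is possible, but it removes only half the problem: delayed effects of training would still be ruled out by date. A classification rule should also not depend on a reader taking a broad term in a narrow sense.

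A second argument is that a journal article condenses the full protocol. That excuses missing detail on adverse event forms. It does not excuse a rule that is stated without exception.

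Other counter-arguments succeed, and they limit the point. A reader might infer the following, which the document does not support:

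- **That the rule biases the comparison of safety between arms.** The safety outcome counts events by when they occur, in training sessions. A label on later events neither adds to that count nor subtracts from it. Restricting the outcome to sessions is a separate choice made in section 2.4.8.
- **That the rule hides events in whichever arm has more early stopping.** Section 2.3 says the intervention "will be modified or discontinued if the drug dose changes in response to harms, the participant requests it, the disease worsens", whereas section 2.9 speaks of having finished it. Nothing equates the two, so differential loss is conjecture.
- **That the data monitoring committee would be misled.** Section 2.9 says the committee advises on changes to trial intake. It does not say the committee relies on relatedness judgements.
- **That events go unrecorded.** They are registered regardless of cause, and no end to registration is stated.
- **That the post-test is a maximal test by the protocol's own description.** The article describes an incremental test for VO2peak. The point needs only that it is a study procedure.

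**Conclusion.** The concern holds as a wrongly stated classification rule. As written, section 2.9 labels post-test events and delayed events after the last session as not caused by a study procedure, without assessment, and it conflicts both with the schedule in section 2.4 and with the narrower pre-intervention rule beside it. The consequence is an unreliable relatedness classification, and so an unreliable overall safety account, for up to 60 post-tests and the interval leading to each.

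This rests on two readings. The first is that the intervention means the 8-week training programme, which section 2.3 supports. The second is that the study protocol procedure includes the study's own tests, which is the plain meaning. If the second is given up, the conclusion shrinks to delayed training effects but does not vanish.

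The primary outcome, sample size, main analysis and in-session safety count are not affected. The rule should be corrected, but it is not a defect that must hold up the trial.

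**What to change.** Delete the automatic post-intervention rule from section 2.9. In its place, state that relatedness is assessed case by case for events through the post-test visit, with two separate judgements: relation to the exercise programme, and relation to a study test procedure (treadmill test or blood draw, before or after training). Keep the pre-intervention sentence, limited as now to the exercise programme, so that a pre-test event can still be attributed to the test. Report both judgements by arm, alongside the section 2.4.8 count and not in place of it. With the calendar rule gone, the meaning of having finished the intervention no longer decides any event's label.

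The cost is one amended paragraph and one additional field on the adverse event form. No visit is added, because the post-test is already scheduled. The reported number of related events may be less favourable than under the present rule.

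### Section 2.9 rules out causality by date although a study treadmill test follows the intervention, calls complaints serious without any threshold, and Section 2.4.8 counts only in-session events

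*Protocol article*

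**What the plan says.** **Seriousness (Section 2.9).** "For this study, sickness, loss of consciousness, weakness, chest pain, or other acute pain will be considered serious adverse events". The sentence attaches no severity or outcome condition to any of these symptoms.

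**Causality (Section 2.9).** Two date rules apply. For an event between consent and the start of the intervention, "it will be considered as not related to the study"; the sentence goes on to name the exercise programme. For an event "after the subject has finished the intervention, it will likewise not be considered to be caused by the study protocol procedure".

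**Study tests (Section 2.4).** "The treadmill test and blood sample collection will be carried out by the cardiologist one week before and after the intervention". The primary outcome, VO2peak, is "obtained in an incremental treadmill test".

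**Safety outcome (Section 2.4.8).** "Safety will be measured as the number of adverse events occurring during the training sessions". Of the events, the section says "these will be recorded as mild, moderate, or severe", and adds that their relation to the session will be considered.

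**Registration (Section 2.9).** Adverse events are defined whatever their cause and are registered from signed consent.

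**Hypothesis (Introduction).** Hypothesis (ii) expects HRV-guided training to be safer than HIIT, so safety is compared between the arms.

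**The concern.** Each rule departs from what a safety comparison needs.

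- A calendar rule replaces a judgement on the individual event. It does so in a period that contains a study procedure and directly follows the last training sessions.
- A symptom list without a threshold gives trivial and grave events the same serious label, so the label no longer separates them.
- The outcome window is narrower than the registration window. The trial collects information on events outside sessions and then leaves it out of the comparison that is meant to use it.

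At stake are the correct labelling of events near the end of the study and the completeness of a between-arm safety comparison. The article states these rules outright, so they are not details left to a fuller document.

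**Working it through.** The article gives no safety figure to reproduce. The check sets the rules side by side, with one piece of arithmetic on the size of the counting window.

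**Step 1: follow an event through the rules according to when it occurs.**

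| When the event occurs | Causality under 2.9 | In the 2.4.8 safety outcome? |
|---|---|---|
| After consent, at the baseline treadmill test | Ruled unrelated to the exercise programme; link to the test not addressed | No |
| During a training session | No date rule; 2.4.8 considers the relation to the session | Yes |
| Between sessions, during the 8 weeks | No date rule | No |
| After the last session, before the post-test | Ruled not caused, by date | No |
| At the post-test treadmill test or blood sampling | Ruled not caused, by date | No |

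Events in every row come under registration: Section 2.9 starts it at consent, and its rule for events after the intervention presupposes that they are recorded.

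**Step 2: the last two rows.** The post-intervention rule refers to the study protocol procedure. The pre-intervention rule refers only to the exercise programme, so the later rule is the broader in its wording. Taken literally, an event during the post-test is declared not caused by a protocol procedure while one is being performed. An event in the days after the last session is excluded as well. Table 1 puts HIIT-G's highest intensities in weeks 7 and 8, so a delayed effect of the last sessions cannot be dismissed in advance.

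**Step 3: seriousness.** Take a mild acute pain in a session. Section 2.4.8 grades it mild; Section 2.9 makes it serious, because any acute pain qualifies. The same holds for mild weakness or sickness. Nothing in the sentence prevents this.

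**Step 4: size of the counting window.** Inputs from Section 2.3: 8 weeks, 3 sessions a week, 1 hour a session.

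- Session time per patient, at most: 8 × 3 × 1 h = 24 h. The 24 sessions agree with S1–S24 in Table 1.
- Length of the intervention period: 8 × 7 × 24 h = 1,344 h.
- Share covered by the safety outcome: 24 / 1,344 = 0.0179, about 1.8%.

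This is a share of time, not of events. Events may well cluster in sessions, so it does not estimate the fraction missed. But the article gives its own reason to look beyond the session: the Introduction cites a finding that in stroke patients HRV had not returned to baseline 30 minutes after exercise, whereas the cooldown in Section 2.3 lasts 10–12 minutes.

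**The case against.** **What stands.**

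- A reader might infer that the serious label decides hypothesis (ii). It does not. The outcome in Section 2.4.8 counts adverse events of any kind during sessions, and no outcome, analysis or stopping rule in the article uses the label. Minor complaints also remain identifiable by their grade.
- A reader might see a contradiction between the mild/moderate/severe scale and the serious list. Severity and seriousness are different attributes, so having both is not an error; the fault is the missing threshold. That the list does not name death, hospital admission or a new stroke is no finding either: the sentence does not say the list is exclusive, and a condensed article may leave the general definition to the full protocol.
- Events between sessions are registered, and no rule calls them unrelated. They are left out of one outcome, not lost.
- The post-test is the same in both arms, so omitting its events does not by itself favour HRV-G. The article calls the test incremental, not maximal.
- A reader might infer that a raw count flatters HRV-G because rest days reduce exposure. Figure 1 offers low intensity or rest and gives no number of rest days, so no reduction can be calculated. With equal arms, a raw count corresponds to events per randomised patient, and fewer sessions may be part of the strategy being compared. Nor does HIIT-G always train hard: weeks 1 and 2 are a lower-intensity period common to both arms, and HRV-G also trains at high intensity when HRV is in its normal range.

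**What does not rescue the rules.** The word linking the two date rules could mean that the second, like the first, concerns only the exercise programme. On that reading post-test events are merely unaddressed, but delayed effects of the last sessions are still excluded by date. In-session safety is a defensible target for a supervised programme, but that supports keeping it as a subset, not as the whole outcome. The relation to the session considered in Section 2.4.8 concerns events in sessions and does not reach those after the intervention.

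**Conclusion.** The point holds as a fault in three stated rules. As written, Section 2.9 would label post-test events, and delayed events after the last session, as not caused by the protocol without looking at them. It would give mild complaints the serious label. Section 2.4.8 would confine the safety comparison to at most 24 hours per patient, about 1.8% of the intervention period, although events are registered from consent.

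The number of events affected cannot be calculated, because the article gives no event rates; the direction of any effect on the between-arm comparison is likewise not established. The post-test part rests on the literal wording of the post-intervention rule; the part on delayed effects holds on either reading. Safety is a secondary outcome and the primary VO2peak analysis is untouched. This is a worthwhile correction to safety labelling and reporting, not a defect that threatens the trial's main conclusion.

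**What to change.** Reconcile Sections 2.4, 2.4.8 and 2.9.

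1. **Causality (2.9).** Replace both date rules with a case-by-case judgement that considers the training sessions and the study tests as possible causes.
2. **Seriousness (2.9).** Define serious by the outcome of the event. Keep the listed symptoms as events of special interest, graded mild, moderate or severe as in 2.4.8.
3. **Counting window (2.4.8).** Report by arm all events from the first study test to the end of the post-test, per randomised patient. Show in-session events as a subset and the number of sessions attended alongside.

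The cost is changed wording in the protocol and case forms and slightly more event review. No extra visits or measurements are needed, since events are already registered from consent.

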Therefore, HRV is a biomarker that can indicate the health status of the cardiovascular system, serving as an effective tool for individualizing the training load in cardiac patients. Moreover, it can be used to measure cardiovascular responses to therapeutic interventions, with HIIT-based exercise being the most recommended option. However, with the goal of obtaining improved results regarding cardiovascular rehabilitation, it is still unclear whether to opt for HIIT training or to individualize HIIT training using HRV. We hypothesize that (i) both HIIT training and HRV-guided training will improve cardiorespiratory fitness, functional performance, heart rate variability, relative weight and fat distribution, inflammatory markers, cognitive function, and quality of life in post-stroke patients but that HRV-guided training will achieve better results; and (ii) HRV-guided training will be safer and more feasible and will generate more patient adherence to the program. The primary objective of the proposed protocol is to determine the effect of HIIT- compared to HRV-guided training on cardiorespiratory fitness in post-stroke patients who undertake an 8-week cardiac rehabilitation program. The secondary aims of this trial are (i) to determine the effect of HIIT training compared to HRV-guided training on heart rate variability scores in post-stroke patients, (ii) to investigate the effect of each exercise program in terms of the adaptations obtained in functional parameters, body composition, and the quality of life of these patients, (iii) to study the effect of both programs on inflammatory markers, (iv) to determine which exercise program is more effective at improving cognitive function, and (v) to analyze whether the two exercise programs are equally feasible and safe, as well as to evaluate their effect on patient adherence to the cardiac rehabilitation program.

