## Figures and Tables

**Figure 1 ijerph-19-10868-f001:**
[figure not shown]
HRV-guided training schema [36]. When LnrMSSD7-d is within the normal range, high-intensity training sessions will be prescribed. If LnrMSSD7-d falls below the normal range, low intensity or rest will be prescribed. Low = exercise at 65% of maximal heart rate, High = exercise at 85% more of maximal heart rate, Rest = resting day, HRV+ = increased or unchanged HRV; HRV− = decreased HRV.

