**Figure 2 ijerph-19-10868-f002:**
[figure not shown]
Schedule of enrolment, interventions, and assessment. HRV-G = heart-rate-variability-based training group; HIIT-G = HIIT-based training group.

**Table 1 ijerph-19-10868-t001:** Periodization and training distribution for HIIT-G.

**Period**	**Week**	**Day/Date**	**Session**	**Time**		**Intensity**		**Continuous Training**
FP	1	Day 1	S1	25′–30′		65–70% max HR RPE 6–7		
		Day 2	S2					
		Day 3	S3					
	2	Day 4	S4	30′–35′		70–75% max HR RPE 6–7		
		Day 5	S5					
		Day 6	S6					
**Period**	**Week**	**Day/Date**	**Session**	**Time**		**Intensity**		**Intervals**
				**W**	**Rest**	**W**	**Rest**	
TP	3	Day 7	S7	1′30″	1′30″	85% max HR RPE 8–10	60–70% max HR RPE 5–6	8
		Day 8	S8					8
		Day 9	S9					8
	4	Day 10	S10	1′30″	1′30″	85% max HR RPE 8–10	60–70% max HR RPE 5–6	8
		Day 11	S11					8
		Day 12	S12					8
	5	Day 13	S13	1′30″	1′15″	90–95% max HR RPE 9–10	60–70% max HR RPE 5–6	8
		Day 14	S14					8
		Day 15	S15					8
	6	Day 16	S16	1′30″	1′15″	90–95% max HR RPE 9–10	60–70% max HR RPE 5–6	9
		Day 17	S17					9
		Day 18	S18					9
	7	Day 19	S19	1′30″	1′	95–100% max HR RPE 9–10	60–70% max HR RPE 5–6	9
		Day 20	S20					9
		Day 21	S21					9
	8	Day 22	S22	1′30″	1′	95–100% max HR RPE 9–10	60–70% max HR RPE 5–6	9
		Day 23	S23					9
		Day 24	S24					9

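### Seriousness of adverse events is set by a symptom list with no threshold and no outcome criterion, and is not linked to the mild/moderate/severe grade, so a serious-event tally by arm would mix exertional symptoms with harm

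*Protocol article*

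**What the plan says.** - **Seriousness (section 2.9).** "For this study, sickness, loss of consciousness, weakness, chest pain, or other acute pain will be considered serious adverse events". This is the only criterion for seriousness in the article.
- **Adverse event (section 2.9).** "An adverse event will be considered any untoward medical occurrence involving a subject, regardless of the possibility of a causal relationship". Registration starts at signed consent.
- **Grade (section 2.4.8).** Of adverse events: "these will be recorded as mild, moderate, or severe". The same section adds that "their relation to the exercise session will also be taken into account". It does not say how grade and seriousness relate.
- **Safety outcome (section 2.4.8).** "Safety will be measured as the number of adverse events occurring during the training sessions".
- **Hypothesis (Introduction).** The second of the two hypotheses includes that "HRV-guided training will be safer and more feasible".
- **Prescribed effort.** For HIIT-G, Table 1 rises to "95–100% max HR RPE 9–10" in weeks 7 and 8. For HRV-G, the Figure 1 legend states: "If LnrMSSD7-d falls below the normal range, low intensity or rest will be prescribed".

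**The concern.** The list works badly in two directions.

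It takes in too much. Weakness and acute pain are common, non-specific effects of hard exercise, and nothing requires them to be intense, lasting or consequential before they count as serious.

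It also takes in too little. The trial enrols post-stroke patients, yet the list names no outcome: not death, threat to life, hospital admission, lasting disability or recurrent stroke.

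At stake is the meaning of any serious-event count that the trial reports. The Introduction motivates individualised training partly by the serious adverse events that still occur in cardiac rehabilitation, and it predicts that one arm will be safer. A reader will therefore look for serious events by arm. The arms are also prescribed different effort, so a label that responds to exertion can differ between them without any difference in harm, or can bury a real difference.

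**Working it through.** The plan gives no figure to reproduce on this point. The check is a comparison of sections, followed by an illustration with assumed rates.

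**How the rules classify four events**

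| Event | Adverse event (2.9) | Serious (2.9 list) | In the safety count (2.4.8) |
|---|---|---|---|
| Brief, mild weakness in a session | yes | yes | yes |
| Chest pain in a session | yes | yes | yes |
| Arrhythmia in a session leading to admission, no listed symptom | yes | no | yes |
| Recurrent stroke with speech loss, at home between sessions | yes | no | no |

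The first and last rows show the problem: the mild event is serious and counted, while the grave one is registered but neither serious nor counted. The safety-count column does not depend on the serious column, so relabelling events leaves the stated safety outcome unchanged.

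**Effort by arm.** HIIT-G is set at RPE 8–10 in weeks 3–4 and RPE 9–10 in weeks 5–8 (Table 1). HRV-G trains at high intensity when its HRV is in range and drops to low intensity (65% of maximal heart rate) or rest when it is below range (Figure 1 legend). The first two weeks are common to both arms. The realised difference in effort is unknown, but a difference is built into the design.

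**Illustration: what a serious-event tally could do**

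Inputs from the protocol: 30 patients per arm (section 2.5) and significance level 0.05 (section 2.8), taken as two-sided. All event rates below are assumptions; the protocol gives none.

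Let h be the proportion of patients with real harm and e the proportion with an exertional symptom on the list, taken as independent. The proportion with at least one event counted as serious is p = 1 − (1 − h)(1 − e). With p̄ the mean of the two proportions, the chance of a significant difference in one direction is Φ[(|p1 − p2| − 1.96·SE0)/SE1], where SE0 = √[2p̄(1 − p̄)/30] and SE1 = √[p1(1 − p1)/30 + p2(1 − p2)/30].

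Worked case, h = 5% in both arms, e = 40% in HIIT-G and 20% in HRV-G:
- p1 = 1 − 0.95 × 0.60 = 0.43
- p2 = 1 − 0.95 × 0.80 = 0.24
- chance of a significant result favouring HRV-G: 34%
- share of HIIT-G patients counted as serious who had real harm: 0.05/0.43 = 12%

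Equal real harm in both arms, h from 2% to 10%:

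| Exertional symptoms, HIIT-G vs HRV-G | Chance of significance favouring HRV-G | Share of HIIT-G serious cases with real harm |
|---|---|---|
| 20% vs 10% | 13–17% | 9–36% |
| 40% vs 20% | 30–37% | 5–22% |
| 60% vs 30% | 55–63% | 3–16% |
| 30% vs 30% | 2.5% (nominal) | 6–27% |

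The reverse case is a real difference in harm, 20% vs 2%, with the same symptom rate in both arms:
- e = 0%: 0.20 vs 0.02, power 61%
- e = 30%: 0.44 vs 0.314, power 17%
- e = 60%: 0.68 vs 0.608, power 8%

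Unequal symptoms can create a difference, and equal symptoms can hide one.

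**The case against.** The strongest reply is that the protocol plans no comparison of serious events. Section 2.4.8 counts all adverse events in sessions, and that count is indifferent to the label. This stands. A reader might infer that the definition tilts the trial's stated safety result against HIIT-G; the documents do not support that. The illustration concerns a tally that someone might report, not a specified endpoint, and its tilt comes from an assumed two-to-one symptom ratio.

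Three further replies also stand, in whole or in part.

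- **No strict contradiction.** Severity and seriousness are separate attributes, and one event can carry both. A reader might say that sections 2.4.8 and 2.9 conflict. They are unlinked, which is less than that.
- **Not only effort symptoms.** Loss of consciousness and chest pain are on the list, and each event's relation to the session is recorded. To say that a serious count would measure effort and not harm goes too far; it would measure both.
- **Grave events are still registered.** The broad adverse event definition covers them, and those occurring in sessions enter the safety count. A reader might infer that they vanish; the documents do not say so. Nor does the text state that the list is exhaustive, and sickness is undefined and might be read widely.

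A broad list may also be a deliberate precaution, and an article may leave reporting forms to a fuller document. That does not remove the point. The sentence in section 2.9 is an explicit trial-specific rule, not a detail left out, and caution does not explain a list that names no outcome.

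**Conclusion.** The concern holds in a limited form. Followed as written, section 2.9 makes mild exertional symptoms serious, and it withholds the label from an admission or recurrent stroke that shows no listed symptom. Where such an event occurs outside a session, it also falls outside the section 2.4.8 safety count.

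The defect lies in classification. The primary outcome and the stated count of session adverse events are unaffected. What is lost is the interpretability of any serious-event count given by arm or cited for the safer claim.

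The size cannot be fixed from the documents. The range of 13% to 63% for a spurious finding, and the fall in power from 61% to 17% or 8%, depend wholly on the assumed rates, on independence of harm and symptoms, and on someone making that comparison. What does not depend on those rates is that the list mixes exertional symptoms with harm while prescribed effort differs by arm.

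**What to change.** Reconcile sections 2.4.8 and 2.9 as follows.

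1. Define a serious adverse event by outcome: death, a life-threatening event, new or prolonged hospital admission, lasting disability, or another medically important event such as recurrent stroke.
2. Keep recording the five listed symptoms as adverse events, graded mild, moderate or severe as in section 2.4.8. Loss of consciousness and chest pain may still qualify as medically important.
3. State that grade and seriousness are recorded separately for each event.
4. Report serious events by arm over the whole intervention period, in or out of sessions, alongside the existing count of all session adverse events.

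The cost is one amended sentence in section 2.9, a line in section 2.4.8 and a change to the adverse event form. The number of events called serious will change. If events have already been recorded, they need reclassifying, preferably by someone unaware of the arm.
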